## 11.2 Randomization

Randomization of two of the study arms (group A and group C) will be performed in a 1:1 ratio stratified by 1) study site and 2) sex (male/female).

The randomization code will be generated by the study statistician using permuted blocks and implemented into the electronic CRF system (Askimed) in a two-step process using an external randomization tool or paper based. Patients will be randomized after verification of inclusion and exclusion criteria as well as stratification status and after screening assessments have been performed. Randomization code will be strictly blinded to clinical investigators and participants in Arms 1 and 2 for 90 days after the boost.

For the T cell determination sample, only participants from the Innsbruck trial site will be included to prevent poor cell quality due to sample transport. The first 100 samples at Innsbruck trial site in each of the three arms will be selected for T cell analysis.

Following the third immunization between day 200 and 260, 100 subjects will be selected for T cell analysis. Preferentially, subjects for which the T cell response had already been determined after boost immunization will be selected.

## 11.3 Statistical Design, Methods and Analysis process

### 11.3.1 Study Design

This is a multi-center, single-blinded, three-arm, randomized clinical trial in a parallel group design, after discontinuation of the homologous Vaxzevria arm a multi-center, non-blinded, two-arm, non-randomized clinical trial in a parallel group design.

### 11.3.2 Definition of Analysis Populations

The following populations will be used for statistical analysis

#### Safety population

The safety population will include all patients who received at least one boost vaccination. In the safety analyses, patients will be analysed by vaccine received, regardless of any errors of dosing or vaccine administration.

#### Intention-to-treat population

The intention-to-treat (ITT) population will consist of all patients. Analyses of this population will assign patients the vaccine they were scheduled to receive.

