|                                           | 
 
6. Subjects with previous positive PCR-test result for SARS-CoV-2 or positive anti-SARS-CoV-2 N protein antibody test
 
7. History of leukemia, lymphoma, or underlying bone marrow disorder (eg, myelodysplasia, myeloma, myeloproliferative disorder) or history of bone marrow transplant.
 
8. Malignancy that required treatment with chemotherapy, immunotherapy, radiation therapy, or other antineoplastic target therapies within 24 months prior to study enrollment.
 
9. Has participated in an interventional clinical study within 30 days prior to study inclusion
 
 
Subjects are excluded from the third dose of vaccination if any of the following criteria apply in addition to the above mentioned ones:
 
 
1. Participant already received a third dose of vaccination.
 
2. Subjects with positive PCR-test result for SARS-CoV-2 after study enrolment or a positive anti-SARS-CoV-2 N antibody test on day 180.
 
 |
| Methodology of the study           | 
Prospective controlled randomized study on vaccination against SARS-CoV-2; after an interim analysis the study is continued as a non-randomized study. Participants that have already been enrolled will be followed until day 180. New participants are only enrolled into Group A and Group B.
 
Dosage BNT162b2: 30µg/0.3ml/injection
 
Dosage ChAdOx1-S: 5x10^10 viral particles /0.5ml/ injection
 
The study includes 3 arms:
 
Group A (randomized): ChAdOx1-S prime and BNT162b2 boost 12 weeks (± 1 week) between prime and boost. Until the interim analysis this group had been randomized. Following interim analysis new participants will be enrolled in a non-randomized, non-blinded fashion.
 
Group B (non-randomized): 2 Doses of BNT162b2, 4 - 6 weeks between prime and boost
 
Group C (randomized): 2 Doses of ChAdOx1-S, 12 weeks (± 1 week) between prime and boost. Recruitment of new participants is discontinued for this group after interim analysis.
                                       |

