## 4.1 Number of Patients

A total of 2124 subjects will be included in this study. Each arm of 1000 subjects will be vaccinated as it follows:

Group A: ChAdOx1-S prime and BNT162b2 boost

Group B: BNT162b2 boost prime and BNT162b2 boost

Group C: ChAdOx1-S prime and ChAdOx1-S boost (this arm has been closed after 124 subjects have been randomized to; therefore, the total number of subjects is reduced from 3000 to 2124).

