### 11.3.5 Data Analysis

#### Efficacy analysis

Efficacy analyses are performed for the comparison of neutralizing titers against the wild type and escape variants at 30 days (primary endpoints of the study) and on breakthrough

infections of wild type/ escape variants (secondary endpoint) at 180 days. The main efficacy analysis is performed between the two randomized arms (Arm C: ChAdOx1-S prime & boost; Arm A: ChAdOx1-S prime and BNT162b2 boost).

Neutralising titer and breakthrough infection are both defined as binary quantitative variables.

Hypothesis testing between the two treatment arms will be performed using Chi testing and logistic regression including stratification variables.

Efficacy analyses will be performed on the ITT and PP populations. The analysis of the ITT population will be considered as the primary analysis. All statistical tests are two-sided with a significance level of 0.05.

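### The primary A versus C analysis set is not limited to randomised participants, so Group A participants enrolled openly after Group C closed would enter it

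*Protocol*

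**What the plan says.** All references are to the protocol.

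- **Analysis set (11.3.2).** "The intention-to-treat (ITT) population will consist of all patients". Assignment follows the planned vaccine: "Analyses of this population will assign patients the vaccine they were scheduled to receive". The per-protocol set requires the boost and compliance to day 30. It does not require randomisation either.
- **Comparison (11.3.5).** "The main efficacy analysis is performed between the two randomized arms", named there as C and A. It covers neutralising titres at 30 days and breakthrough infections at 180 days. "The analysis of the ITT population will be considered as the primary analysis".
- **Method (11.3.5).** Chi-square "testing and logistic regression including stratification variables". The Synopsis names these variables as study site and sex. "All statistical tests are two-sided with a significance level of 0.05".
- **Who is in Group A (Synopsis, Methodology of the study).** The group is still labelled as randomised, but "Following interim analysis new participants will be enrolled in a non-randomized, non-blinded fashion". Sections 3.1 and 6.8 say the same of the second recruitment phase.
- **Size.** Section 4.1 says of Group C that "this arm has been closed after 124 subjects have been randomized to". The Synopsis allows up to 1000 in each of the other two arms.

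**The concern.** Since the interim analysis, Group A has held two cohorts under one label: participants randomised and blinded at the same time as C, and participants given the heterologous boost openly after C had stopped recruiting. The definitions of the analysis sets were not adapted. Followed as written, the comparison that the protocol presents as randomised would consist mostly, on the A side, of people who never had a chance of being allocated to C.

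For breakthrough infection this matters directly. Section 11.1 speaks of falling infection rates in Tyrol and of a variant outbreak that cannot be predicted. Section 1.3 expects a low summer followed by a winter wave. Later enrolment therefore means a different exposure period, and no term for recruitment phase or calendar time is specified. A difference between periods would be read as a difference between vaccines, under an ITT label.

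**Working it through.** **1. The protocol's own power figure.** Section 11.1: 58% versus 65.5%, 1000 per arm, two-sided 5%, power above 90%. With p̄ the pooled proportion,

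s0 = √[p̄(1−p̄)(1/nA + 1/nC)], s1 = √[pA(1−pA)/nA + pC(1−pC)/nC], power = Φ[(|pA−pC| − 1.96·s0)/s1].

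Here p̄ = 0.6175, s0 = 0.02173 and s1 = 0.02167, so power = Φ[(0.075 − 0.0426)/0.02167] = Φ(1.495) = 93.3%. For 58% versus 68% it is 99.6%. The stated figures reproduce, but only for 1000 randomised per arm.

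**2. How many of Group A would be non-randomised.** The number randomised to A is not given.
- Central assumption: 1:1 allocation (11.2) and 124 in C give about 124 in A.
- Lower bound: 106 heterologous participants had reached day 30 at the interim (1.3). That section prints the vaccine order reversed; I take it to mean Group A, the only heterologous arm.
- Upper bound: about 300 recruited in all (1.3), so 300 − 124 (C) − 13 (B at day 30) = 163.

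| Randomised A | Later A if A reaches 1000 | Share |
|---|---|---|
| 106 | 894 | 89% |
| 124 | 876 | 88% |
| 163 | 837 | 84% |

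**3. What pooling can do.** Suppose there is no true vaccine difference, and the 876 later A participants differ from everyone else by δ for reasons of period or selection. The δ values are assumptions; the protocol gives none. The pooled A rate is p + 0.876δ, tested on 1000 versus 124.
- Responders, p = 58%: the nominal 5% test rejects about 9% of the time for δ = 3 points, 16% for 5 points and 49% for 10 points. Worked for 5 points: difference 0.0438, s0 = 0.0462, true standard error 0.0469; Φ[(0.0438 − 0.0906)/0.0469] + Φ[(−0.0438 − 0.0906)/0.0469] = 0.159 + 0.002.
- Infections, p = 1%: the same approximation gives about 12% for δ = 2 points and 43% for 4 points. Only 1.24 infections are expected in C, so I also summed the exact binomial probabilities of all outcomes that the uncorrected chi-square test rejects. This gives about 8% and 46%.

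**4. Power of the restricted comparison, C = 124.**

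| A | 58% vs 65.5% | 58% vs 68% |
|---|---|---|
| 106 randomised | 21% | 34% |
| 124 randomised | 23% | 37% |
| 163 randomised | 25% | 42% |
| 1000 pooled | 38% | 60% |

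The pooled row is valid only if the later cohort is exchangeable with the randomised one.

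**The case against.** The best case against is that the protocol does not intend to pool. Section 11.3.5 speaks of the two randomised arms. Section 11.3.1 describes two stages, the second of which has no Group C. The Synopsis and section 1.3 give the purpose of further recruitment as breakthrough infections in the heterologous against the homologous Comirnaty group. This makes an intention to keep the stages apart plausible. It does not settle the point: the phrase names arms, the Synopsis keeps the label randomised for the mixed Group A, the ITT set takes everyone, and 11.3.5 still makes A versus C the main analysis of breakthrough infection.

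Three stronger readings are tempting, and the documents do not support them.

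- *That the decision to close C was compromised.* The interim titre result (p < 0.001) came before any open enrolment.
- *That randomisation and blinding are lost altogether.* The randomised participants stay identifiable and can be analysed alone. Participant blinding was due to end at day 90 in any case (6.8, 11.2), and titre is a laboratory measurement.
- *That C becomes a historical control.* It belongs to the same trial and is followed for 180 days, so its follow-up can overlap in calendar time with later A. Partly non-concurrent is the accurate term.

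Section 11.1 also already calls the breakthrough comparison underpowered. That stands, but low power does not remove bias.

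**Conclusion.** The point holds. As written, the primary and per-protocol sets admit non-randomised, open-label Group A participants to the main A versus C comparison, and none of them has a C participant enrolled concurrently. If A reaches its cap they would be 84% to 89% of the arm (837 to 894 of 1000), given 106 to 163 randomised to A. Because 1000 is a maximum, these shares are ceilings. The exposure lies in the final titre analyses and chiefly in the 180-day breakthrough-infection comparison. The size of any bias cannot be derived from the protocol; the rejection rates above only show that moderate cohort differences are enough to mislead. This is a rule that is wrong as stated, not detail left to a later plan.

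**What to change.** - In 11.3.2, define the A versus C set as all participants randomised between A and C up to closure of C, analysed as randomised, with a matching per-protocol subset.
- In 11.3.5, use that set for every A versus C analysis, both titres and breakthrough infection.
- Define a separate, explicitly non-randomised A/B cohort (all of A and all of B) with a flag for enrolment phase, for the A versus B comparisons.
- In 11.1, state that 1000 per arm with power above 90% no longer describes A versus C, and give the number actually randomised to A with the resulting power.

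The text change is a few sentences. The real cost is precision: with about 124 per arm, power for 58% versus 65.5% is about 23% (21% to 25%), against a nominal 38% with pooling. The extra 15 points (38 − 23) are bought with participants who are not comparable by design, so giving them up is the right trade.

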#### Per-protocol population

The per-protocol (PP) population will include all patients who received the boost vaccination and fulfilled requirements up to day 30 after the boost. Major protocol deviations will be determined and documented prior to database lock.

#### T cell determination population

The first 100 participants at Innsbruck study site will be selected in each arm for T cell determination. T cell responses will be analyzed in all non-responders after the third vaccination and for 100 subjects in each group after the third vaccination following completion of the follow-up period of 180 days.

### 11.3.3 Interim Analysis

Two interim analyses are scheduled applying the Haybittle Peto rule for early stopping . The first interim analysis will be performed on day 30 for safety and efficacy when n=200 patients have been randomized. The second interim analysis will take place on day 30 after n=400 patients have been randomized. The trial may be stopped early for efficacy regarding the primary endpoint (level of neutralizing antibodies) when the p-value between the two randomized arms is smaller than 0.001 at either the first or the second interim analysis. If one of the two randomized arms is inferior, this arm will be closed and the study will continue in an open, non-blinded and non-randomized design.

Additionally interim analysis can be requested by the Data Safety and Monitoring Board (DSMB).

The number of individuals eligible and willing to a third vaccination at the two potential time points (between day 90 and 180 or after day 180) cannot be foreseen at this point. Therefore, each participant may be analyzed after reaching day 30 individually and efficacy after second and third vaccine dose will be compared at an individual level (before and after design).

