| Immunogenicity blood draw                                                         |                                                                 |                                                             |  |  | X                                     |                                                                                     | X                                                      |
| Concomitant vaccinations                                                          |                                                                 |                                                             |  |  |                                                   |                                                                                     |                                                                    |
| Concomitant medication                                                            | X                                                               | X                                                           |  |  | X                                                 |                                                                                     |                                                                    |
| AEs and SAEs                                                                      | X                                                               | X                                                           |  |  | X                                                 | X                                                                                   | X                                                                  |
| Vaccination                                                                       | X                                                               |                                                             |  |  |                                                   |                                                                                     |                                                                    |

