| ediary, symptom reporting                                                         |                                                                 | x                                                           |  |  |                                                   |                                                                                     |                                                                    |

 Before vaccination;

 Assessment of antibody against wt and immune escape variants,

 Blood count, coagulation status, CRP, etc.

 Refer to COVID-19 disease observation schedule

 In case of positive Antigen-test

 Participants will be closely observed for at least 30 minutes post-vaccination to monitor for the development of acute reactions. Participants will be allowed to leave the study site after it is documented that the post-vaccination observation period is complete.

 not older than 72 hours before vaccination, alternatively: registered antigen test (not older than 24 hours before vaccination), participants will additionally give a sample for a PCR test at visit I prior to vaccination

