# 2. Study Objectives and Endpoints

## 2.1 Primary Study Objectives and Endpoints

| Primary Objectives                                                                                                                                                                                                            | Primary Endpoints                                                                                                                                                         |
|-------------------------------------------------------------------------------------------------------------------------------------------------------------------------------------------------------------------------------|---------------------------------------------------------------------------------------------------------------------------------------------------------------------------|
| Efficacy Objective
To determine whether the immune response to vaccine SARS-CoV-2 spike protein is at least as effective for the heterologous prime-boost regime Vaxzevria followed by Comirnaty as in the approved | Efficacy Endpoint
1a Level of neutralizing antibodies against wild-type and immune escape variants in the 3 study groups at 10, 30, 90 and 180 days post boost. |

|                                                                                                                                                                                                                       |                                                                                                                                           |
|-----------------------------------------------------------------------------------------------------------------------------------------------------------------------------------------------------------------------|-------------------------------------------------------------------------------------------------------------------------------------------|
| 
homologous Vaxzevria and Comirnaty regimen.
 
To determine immune responses in non-responders after a third immunization
 
To determine immune responses all participants after a third immunization
 | 
1b Level of neutralizing antibodies against wild-type and immune escape variants at 10, 30, 90 and 180 days post 3rd immunization.
 |

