### 4.3 Exclusion Criteria

Subjects are excluded from the interventional part of the study if any of the following criteria apply:

1. Participant has already received full vaccination against SARS-CoV-2
2. Prior administration of an investigational coronavirus (SARS-CoV, MERS-CoV) vaccine or current/planned simultaneous participation in another interventional study to either prevent or treat COVID-19
3. Participant has received/plans to receive a non-study vaccine within 14 days prior to or after any dose of IP (except for seasonal influenza vaccine which is not permitted within x days before or after any dose of IP)
4. Participant has a contraindication to IM injections and blood draws (eg, bleeding disorders)
5. Participant has a known or suspected allergy or history of anaphylaxis, urticaria or other significant adverse reactions to vaccines or their excipients (including specifically the excipients of the study vaccine; refer to the IB)
6. Subjects with previous positive PCR-test result for SARS-CoV-2 or positive anti-SARS-CoV-2 N antibody test
7. History of leukemia, lymphoma, or underlying bone marrow disorder (eg, myelodysplasia, myeloma, myeloproliferative disorder) or history of bone marrow transplant.
8. Malignancy that required treatment with chemotherapy, immunotherapy, radiation therapy, or other antineoplastic target therapies within 24 months prior to study enrollment.
9. Has participated in an interventional clinical study within 30 days prior to study inclusion

Subjects are excluded from the third dose of vaccination if any of the following criteria apply in addition to the above mentioned ones:

3. Participant already received a third dose of vaccination.
4. Subjects with positive PCR-test result for SARS-CoV-2 after study enrolment or a positive anti-SARS-CoV-2 N antibody test on day 180.

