#### 5.10.2 SARS-CoV-2 RT-PCR-testing

Weekly antigen or RT-PCR tests have to be performed starting on Day 7 until Day 182 after boost shot.

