#### 5.12 Visit I – 3rd vaccination

All subjects will receive the third dose with **Comirnaty (BNT162b2)**.

Before IMP injection the following assessment should be performed:

- SARS-CoV-2 PCR Test (not older than 72 hours before vaccination)

- Alternatively: registered antigen test (not older than 24 hours before vaccination), participants will additionally give a sample for a PCR test at visit I prior to vaccination, in case this PCR test is positive the participant will be excluded after vaccination

After IMP injection AEs the subject will be observed for 30 minutes and all AEs/SAEs will be recorded.

Participants should seek immediate medical attention if they develop symptoms such as

- shortness of breath
- chest pain
- leg swelling
- persistent abdominal pain following vaccination
- neurological symptoms including severe or persistent headaches and blurred vision
- skin bruising (petechial) beyond the site of vaccination after a few days

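### Third-dose endpoint 1b: the before-and-after comparison names no before sample, no antibody draw is scheduled at the dose, and the Day 180 anti-N exclusion comes too late for the Day 110–180 group

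*Protocol*

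**What the plan says.** Section 2.1 lists as a primary endpoint "1b Level of neutralizing antibodies against wild-type and immune escape variants at 10, 30, 90 and 180 days post 3rd immunization". All eligible participants receive the same third vaccine (section 5.12), so nobody serves as a concurrent control. The only analysis described is in section 11.3.3, which says that "efficacy after second and third vaccine dose will be compared at an individual level (before and after design". On timing, the same section offers only that "each participant may be analyzed after reaching day 30 individually".

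The third dose is given on Day 110–180 after the boost to participants without neutralizing antibodies on Day 90, and on Day 200–260 to all others (sections 4.2 and 5.11).

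In the visit plan after the third vaccination, the row "Immunogenicity blood draw" is marked only at Day 10 and at Days 30, 90 and 180 after the dose. The Visit I cell is empty, and so is the whole antibodies row. The footnote "Before vaccination" is printed under the table, but no cell refers to it. Section 5.12 lists one assessment before injection: "SARS-CoV-2 PCR Test (not older than 72 hours before vaccination", or an antigen test with a PCR sample taken at the visit.

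Infection surveillance after the boost is set in section 5.10.2: "Weekly antigen or RT-PCR tests have to be performed starting on Day 7 until Day 182 after boost shot". Section 4.3 bars a third dose after any positive PCR since enrolment or "a positive anti-SARS-CoV-2 N antibody test on day 180"; the synopsis has the same rule.

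**The concern.** In a before-and-after design, everything rests on the before value. If it is not named, the contrast for a primary endpoint can be chosen once titres are known. If it is an old sample, the change credited to the third dose also contains whatever happened between that sample and the injection. Waning makes the rise look too small. An unrecognised infection makes the response look too large. Both depend on how late in the window the dose was given. The protocol itself raises limited durability of protection as a reason for the study (section 1.3).

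The anti-N rule is the plan's means of finding past infection that PCR missed. A test dated after the injection cannot do that. Once the injection has been given, a pre-dose sample that was not drawn cannot be recovered.

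**Working it through.** **1. Is there a pre-dose sample?** The boost visit plan marks an immunogenicity draw before vaccination at screening, and sections 5.2 and 5.10.4 give it as 9 ml EDTA. The third-dose plan has no screening visit, and its Visit I cell is empty, although other rows of the same table (vaccination, pregnancy test) are marked at Visit I. Section 5.12 agrees with the table. The unused footnote suggests that the draw was lost when the boost table was copied.

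**2. Age of the last scheduled sample at the dose.** Inputs: draws on Day 90 and Day 180, each ±3 days (section 5.8), and the two dosing windows. Age = dosing day − sampling day.

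| Group | Nominal | With ±3 days |
|---|---|---|
| Dose Day 110–180, sample Day 90 | 110−90 = 20 to 180−90 = 90 | 110−93 = 17 to 180−87 = 93 |
| Dose Day 200–260, sample Day 180 | 200−180 = 20 to 260−180 = 80 | 200−183 = 17 to 260−177 = 83 |

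On Days 177–180 the scheduled Day 180 draw could coincide with the dose.

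**3. If Day 30 after the boost is the before value.** Its age at the third dose is 110−30 = 80 to 180−30 = 150 days in the earlier group, and 200−30 = 170 to 260−30 = 230 days in the later group. Matching Day 30 after dose 2 with Day 30 after dose 3 needs no Day-0 titre. It still leaves that interval open to infection.

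**4. Time without scheduled infection testing.** Weekly tests run to Day 182.
- Dose Day 110–180: no gap.
- Dose Day 200–260: 200−182 = 18 to 260−182 = 78 days (16 to 80 with the ±2 day window).

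The PCR at Visit I finds a current infection, and a known positive PCR excludes. What is missed is an infection that was never diagnosed and resolved between Day 182 and the dose.

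**5. Size of that gap.** The only rate available is the illustration in section 11.1. It reproduces: 8 cases per week × 26 weeks = 208; 208 / 416,758 = 49.9 per 100,000; divided by the assumed 5% detection this is about 1000 per 100,000, or 10 per 1000 in 180 days. Applied to the gap: 10 × 18/180 = 1.0 to 10 × 78/180 = 4.3 per 1000. This covers B.1.351 only, at the rate seen when the section was written. No all-variant rate is given.

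**6. The anti-N criterion.** With its window, Day 180 means Days 177–183. A dose on Days 110–176 precedes it in every case: 67 of the 71 days in the earlier dosing window. The anti-N half of the exclusion therefore cannot act there, while the PCR half can. In the later group the test precedes the dose but sees nothing after about Day 180.

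**The case against.** The strongest reply is that section 11.3.3 never says that the comparator is the last pre-dose titre. It speaks of efficacy after the second and after the third dose and names Day 30. On a plain reading this sets Day 30 after dose 2 against Day 30 after dose 3. Both samples are scheduled, and waning before the third dose does not enter as a stale-baseline error. That reading is fair. It moves the fault from a missing sample to an unnamed one, and it does not remove the infection problem.

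A reader might infer more than the documents support:

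- *That the baseline is three months old and infections go unseen in the same people.* The 90–93 day gap belongs only to the Day-90 non-responders. They start without neutralizing antibodies, so there is little to wane, and weekly testing covers their whole pre-dose period. The testing gap exists only in the later group, whose sample is at most 80–83 days old.
- *That the fold rise is understated by a known factor.* With an assumed half-life of 60–120 days, an 83-day-old titre would have fallen to 0.38–0.62 of its value. The protocol gives no half-life and specifies no fold-rise measure, and section 11.3.5 treats titre as binary. No such factor can be claimed.
- *That the trial's main analysis is undermined.* Endpoint 1b is primary, but the sentence stands under Interim Analysis, and section 11.3.5 makes Arm A against Arm C the main efficacy comparison.
- *That the two third-dose groups cannot be compared.* The protocol plans no such comparison.

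One could also argue that section 5.18, which refers back to the boost assessments, carries the pre-vaccination draw over. It does list its departures without naming this one. But there is no third-dose screening visit to hold the draw, and both the table and section 5.12 leave it out.

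**Conclusion.** The point holds within limits and has two parts.

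**Wrong as written:** the anti-N exclusion on Day 180 normally falls after the dose in the Day 110–180 group and cannot screen them. Section 4.3 and the synopsis have to be reconciled with the dosing window.

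**Cheap improvement:** the before value for 1b should be named, and a sample should be drawn at the dose. Without it, the latest scheduled value is 17–83 or 17–93 days old. If that value is used, waning is mixed with the dose effect, chiefly in the Day 200–260 group, by an amount that the documents do not allow one to state. On either comparator, undiagnosed and resolved infections remain in the later group. The estimate of about 1–4 per 1000 rests on the B.1.351 illustration staying constant. Section 1.3 expects a winter infection season with a substantial share of escape variants, so the all-variant figure could differ, but the protocol gives no number for it.

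**What to change.** 1. In section 11.3.3, name the before time point for endpoint 1b: the pre-dose sample, Day 30 after the second dose, or both with one designated as the main contrast.
2. In the third-dose visit plan and section 5.12, add the 9 ml EDTA antibody sample at Visit I before injection and use it as the pre-dose value. This attaches the unused footnote and brings the sample age to 0 days in both groups.
3. Test anti-N on that tube and report anti-N positives separately in the 1b analysis. If no tube can be added, test the Day 10 post-dose sample that is already drawn. Section 6.1 describes both vaccines as encoding spike, so anti-N can still be read as a marker of infection after the dose. This fallback deals with infection only; it gives no pre-dose titre and leaves the waning question open.
4. Reconcile the Day 180 anti-N criterion in section 4.3 and the synopsis with the Day 110–180 dosing window. The choice of rule is for the sponsor.

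Cost: one tube and one assay run per participant at a visit that already takes place, plus amendment wording. The fallback needs no extra blood.
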